## Methods

### Study Design and Setting

This population-based study adopts a test-negative case-control design to analyze COVID-19 VE against symptomatic and fatal SARS-CoV-2 infection from available health care datasets in the Special Capital Region of Jakarta, one of the provinces with the highest population density (15,900 people per km^2^ in 2020) and case rate per population relative to other regions in Indonesia [9]. Despite its robust development and economic growth, the contrast between rich and poor neighborhoods was highly prevalent in many parts of Jakarta’s districts [8,10].

This study will estimate VE against COVID-19 during the period of interest, which were the COVID-19 waves associated with the Delta and Omicron variants, from June 1 to August 31, 2021, and January 1 to April 2, 2022, respectively. Within each of these periods, a cycle of sustained upward and downward trends of the test positivity rate was observed [11-15] (Figure 1). Furthermore, the Delta and Omicron variants were estimated to be responsible for around 90% of SARS-CoV-2 infections in Jakarta during these two periods [14,16].

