**Figure 1 figure1:**
[figure not shown]
Trend of the national COVID-19 positivity rate in Indonesia from 2021 to 2022. This modified image is cited from Our World in Data.

During the Delta and Omicron periods, several brands of COVID-19 vaccines were introduced in Jakarta for vaccine rollout, such as AstraZeneca, SinoVac-CoronaVac Biofarma, Covovax-Novovax, Indovax, Johnson & Johnson, Moderna, Sinopharm BBIBP, and Pfizer (Table S1 in Multimedia Appendix 1) [17]. Among these COVID-19 vaccines, Coronavac-Sinovac was the earliest COVID-19 vaccine to be introduced in January 2021 and used for mass vaccinations of doses 1 and 2, followed by AstraZeneca, Sinopharm, Pfizer, and Moderna in August 2021 [18,19]. Booster vaccinations 6 months after the 2-dose primary vaccination with Moderna and Pfizer vaccines were initially introduced to health care workers in July 2021, followed by the approval of the AstraZeneca vaccine as a booster in the national vaccination program in January 2022 [20,21]. To expedite the booster vaccination coverage, the timeline for booster administration was shortened to 3 months after the 2-dose primary vaccination, and additional inactivated COVID-19 vaccines, such as SinoVac and Sinopharm, were included in the national booster program [22]. Different from Pfizer, Moderna, and AstraZeneca, these inactivated COVID-19 vaccines were only approved as boosters for patients who received similar vaccine platform for their primary vaccination regimen [23]. Until the end of the Omicron period, all of the distributed COVID-19 vaccines in Jakarta were developed from the ancestral strain of SARS-CoV-2.

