### Study Participants

The study will include people 18 years or older who domiciled in Jakarta and underwent an RT-PCR test for SARS-CoV-2 infection due to symptoms of influenza-like illnesses within 10 days of the test date. Although people may have more than one RT-PCR result during the period of interest, this study will only account for the first positive or negative result per person as the index test date for each of the COVID-19 waves. People who had at least one sample with a positive SARS-CoV-2 RT-PCR result during the period of interest will be classified as cases, while people with a negative SARS-CoV-2 RT-PCR without any positive results over the period of interest will be classified as controls.

People with a positive RT-PCR test result within 90 days of the preceding index test date, with inconclusive RT-PCR results, who received different vaccines for dose 1 and dose 2 or a heterologous primary vaccine series, or who had a time interval between dose 1 and dose 2 that was less than the government recommendation (<21 days for Pfizer and Sinopharm, <28 days for CoronaVac and Moderna, and <12 weeks AstraZeneca) will be excluded from the analysis. We will also exclude people with incomplete vaccination records, such as people who declared receiving 2 vaccine doses without being able to verify the previous dose.

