### Study Variables

The primary outcome in this study is symptomatic SARS-CoV-2 infection, defined as a positive RT-PCR test within 10 days from the onset of influenza-like illness. The secondary outcome in this study is fatal SARS-CoV-2 infection, defined as death within 30 days after a positive RT-PCR test result [24]. Meanwhile, the primary exposure in this study was vaccination status, which can be classified as unvaccinated, dose 1 or partial vaccination, dose 2 or primary vaccination, and booster dose. People without any vaccination entries after data linkage with the PCARE Vaksin dataset at the end of each period of interest will be classified as unvaccinated persons. For vaccinated people, we will only consider the last vaccination data entry that happened before the patients’ index RT-PCR test date.

Several covariates should be assessed as potential confounders in the study, such as age in years at the index test date, gender, calendar week of the RT-PCR collection during the period of interest, living in impoverished neighborhoods, presence of any comorbidities, occupation, and reinfection status. The calendar week of the RT-PCR collection during the period of interest will be presented as a whole number starting from week 1 as the start of the period of interest. Living in an impoverished neighborhood will be presented as a dichotomous variable. People will be classified as living in an impoverished neighborhood if their neighborhood number at the subdistrict level is listed as one of the impoverished neighborhoods in the 2018 Jakarta Governor’s regulation concerning improving the quality of settlements in residential areas. Occupation will be presented as categorical variables that consist of health care worker, public or government official, and civilian. Reinfection or people with previous SARS-CoV-2 infections will be presented as a dichotomous variable. People with a previous positive RT-PCR SARS-CoV-2 result that occurred more than 90 days after the current case will be classified as people with a previous SARS-CoV-2 infection [25].

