**Figure 2 figure2:**
[figure not shown]
Study workflow. PCare: Primary Care.

People with data linked to the entries within the Primary Care (PCARE) Vaksin dataset will be classified as vaccinated people (Figure 2). To avoid misclassification of foreigners as unvaccinated people, the study will only use entries with national identity card numbers as ID numbers from each of the study datasets. Vaccinated people with incomplete data on vaccination date and vaccine name will be excluded from the final dataset (Table S2 in Multimedia Appendix 1). From the final dataset, a subset of data containing the matched cases and controls will be created (Table S3 in Multimedia Appendix 1).

As genomic testing was not routinely performed in Indonesia, no data linkage will be performed on the variant dataset. In contrast, the variant dataset, which consisted of the genomic test result of the randomly sampled specimen from the population, will be used to confirm the dominant SARS-CoV-2 variant in Jakarta during each period of interest.

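### The unvaccinated reference group is fixed at the end of the wave, not at the index test, so it is selected on events after the outcome

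*Protocol article*

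**What the plan says.** Study Variables uses two time points for one exposure. Those with no "vaccination entries after data linkage with the PCARE Vaksin dataset at the end of each period of interest will be classified as unvaccinated persons". Among the vaccinated a date limit applies: "we will only consider the last vaccination data entry that happened before" a person's index test. Data Sources adds a rule with no date limit: "People with data linked to the entries within the Primary Care (PCARE) Vaksin dataset will be classified as vaccinated people". The Study Objectives, in contrast, list VE by status when the RT-PCR test was done.

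The waves run "from June 1 to August 31, 2021, and January 1 to April 2, 2022, respectively". Vaccine rollout continued within the first of them: CoronaVac came first, "followed by AstraZeneca, Sinopharm, Pfizer, and Moderna in August 2021".

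Statistical Analysis compares vaccinated with unvaccinated people for both symptomatic and fatal infection, and uses the same reference group for the time-since-vaccination subgroups. Study Participants excludes, among others, people "who received different vaccines for dose 1 and dose 2 or a heterologous primary vaccine series" and people whose two doses were too close together. Neither exclusion is limited to doses given before the test.

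**The concern.** A case-control comparison needs exposure to be read at the same moment, and before the outcome, in everyone. Here a person can lose unvaccinated status through a dose given after the test result is known. If that happens at different rates in cases and controls, the unvaccinated odds are distorted and so is every absolute VE built on them.

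The fatal outcome is the clearest example. People who die within 30 days of a positive test can hardly acquire a later register entry, while living comparators can. The stated safeguards do not address this. Matching on calendar week equalises the time left to the end of the wave, but not vaccine uptake that differs by test result. The 14–90 and 7–90 day windows act only on vaccinated people. Table 3 does not list this bias.

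**Working it through.** The article gives no figure for this bias that could be reproduced. Its sample size is not in dispute. With coverage p0 = 0.20, OR = 0.5 and p1 = 0.10/0.90 = 0.111, the number of cases is 1.96² × 0.5² × [1/(0.111 × 0.889) + 1/(2 × 0.20 × 0.80)]/0.05² ≈ 5,090, with 10,180 controls, against the stated 5000 and 10,000. It does not depend on when status is read.

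**1. Who falls out.** Three kinds of people under the rules as written:
- No entry by the end of the wave: unvaccinated.
- An entry before the test: vaccinated, grouped by the last such dose.
- Only entry after the test but before the end of the wave: not unvaccinated (an entry exists), vaccinated under Data Sources (linked), yet with no dose that counts. No exposure category fits.

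**2. Time available.** Delta: 30 + 31 + 31 = 92 days. Omicron: 31 + 28 + 31 + 2 = 92 days. A first dose can therefore follow the test by up to 91 days.

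**3. Bias factor.** Let a and b be cases vaccinated and unvaccinated at test, and c and d the same for controls. The true OR is ad/(bc). The rule keeps b(1 − p_case) and d(1 − p_control), so

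OR_obs = OR_true × (1 − p_control)/(1 − p_case), and VE_obs = 1 − (1 − VE) × that factor.

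**4. Range for p (assumption).** The article gives no uptake figures. With index dates spread evenly over 92 days, assumed first-dose uptake of 1%, 3%, 5% and 8% per week among the unvaccinated gives p of 6.3%, 17.6%, 27.3% and 39.2%. Values of 6%, 20% and 40% cover this range.

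**5. Death against test-negative controls (p_case ≈ 0).**

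| p_control | Factor | True VE 0% | True VE 50% | True VE 90% |
|---|---|---|---|---|
| 6% | 0.94 | 6% | 53% | 90.6% |
| 20% | 0.80 | 20% | 60% | 92% |
| 40% | 0.60 | 40% | 70% | 94% |

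**6. Symptomatic infection, true VE 50%.**

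| p_control | p_case | Factor | Observed VE |
|---|---|---|---|
| 20% | 20% | 1.000 | 50.0% |
| 20% | 10% | 0.889 | 55.6% |
| 40% | 20% | 0.750 | 62.5% |
| 10% | 20% | 1.125 | 43.8% |

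**7. Death against surviving cases.** At 5% weekly uptake and true VE 50%, with survivors deferring vaccination by 0, 14, 30 or 90 days, the observed VE is 63.6%, 60.1%, 56.6% or 50.0%. At 30 days' deferral the symptomatic estimate is 58.1%, which is above the 56.6% for death.

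**8. Relative VE.** The article's formula reduces to 1 − OR_booster/OR_2-dose. A factor common to both odds ratios cancels, so rVE is largely spared.

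**9. Undated exclusions.** Take a person with dose 1 before the test and a different-brand or early dose 2 after it. Excluding that person removes someone from the dose-1 group. If shares e_case and e_control are removed, the dose-1 OR is multiplied by (1 − e_case)/(1 − e_control). Where controls receive later doses more often than cases, this exceeds 1 and dose-1 VE is pushed down.

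**The case against.** The strongest reply is that the end of the period is only the linkage cut-off, and that status is then assigned at the test. The Study Objectives point that way, and so does the pre-index rule for vaccinated people. No sentence says outright that people first vaccinated after the test are dropped, and the workflow figure and supplementary tables cannot be seen here. This may well be the intent. But the sentence attaches the end of the period to unvaccinated status itself, and the Data Sources rule carries no date, so the text needs correcting on either reading.

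A reader might infer that VE is overstated for every brand, dose, wave and time stratum, and above all for death. The article does not support that. It gives no post-test uptake and does not say that a positive test delays vaccination. Equal uptake gives no bias, and higher uptake in cases understates VE. Nor does it say whether the fatal model compares deaths with test-negative controls or with surviving cases, and step 7 shows that death need not be the worse affected outcome. The undated exclusions can work in the opposite direction for dose 1.

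The size can also be modest. At a true VE of 90%, within the anticipated range, the death estimate moves by 0.6 to 4 points. Omicron began a year after rollout started, so Delta is probably the more exposed wave. That is an inference from the rollout dates, not a documented figure.

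**Conclusion.** The definition is wrong as written. It conflicts with the Study Objectives and lets post-outcome vaccination decide who enters the reference group of every absolute VE analysis.

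- **Death against test-negative controls:** the upward direction follows from the definitions, apart from the rare dose given between test and death. A true 50% reads about 53% to 70% over the assumed range of p_control.
- **Death against surviving cases:** the bias may be smaller, and vanishes if survivors are not vaccinated before the wave ends.
- **Symptomatic infection (primary outcome):** VE is overstated only if cases are vaccinated less or later than controls after the test. Direction and size are otherwise open.
- **Dose-1 estimates:** the undated exclusions may add a downward component.

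All p values are assumptions. The factor is exact for the crude odds ratio; covariate adjustment does not remove selection that depends on the test result.

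**What to change.** Define unvaccinated as no COVID-19 vaccine dose recorded before the index test date, for cases and controls alike, and state that people first vaccinated later stay in this group. Apply the heterologous-series, short-interval and incomplete-record exclusions only to doses given before the index date. Bring Study Objectives, Study Participants, Study Variables and Data Sources into line with this. Both p values are then zero by design, and this source of bias disappears.

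The cost is a few sentences, a date filter in the linkage code and a rerun of any models already fitted. Table 1 lists both vaccination and swab collection dates, and the article reports that analysis was still under way. The required sample size does not change. Counting the people first vaccinated between index test and wave end, by case status, would replace the assumed p values with observed ones at almost no extra effort.

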### Statistical Analysis

We adopted our VE analysis from the Interim Guidance of Evaluation of COVID-19 Vaccine Effectiveness by the World Health Organization, where the final estimate of absolute VE (aVE) will be determined by calculating the adjusted odds ratio (aOR) for vaccination using the formula aVE = (1 – aOR) × 100% [24]. Unconditional multivariable logistic regression will be used to analyze the aOR of having symptomatic and fatal SARS-CoV-2 infection between the unvaccinated and vaccinated participants. We will perform separate analyses for the Delta- and Omicron-dominant periods. Furthermore, within each period, we will also analyze each vaccinated person separately by their vaccine brand or platform and vaccination doses, such as dose 1, dose 2, or booster. For the main aVE analyses, we will include only vaccinated people with the last dose 1 or dose 2 vaccination date within 14-90 days or with the last booster dose within 7-90 days before their index test date and compare them to the unvaccinated people.

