One main logistic model will be assembled by forward inclusion, and only covariates with less than 20% missing data will be considered to be included in the model building. Assessment for confounders and effect modifiers will be performed with the Wald test and by observing the change in the primary exposure coefficient SE. Covariates that act as confounders will be included in the model. If effect modification is present, it is essential to report VE and CIs for each subgroup individually. The linearity between continuous variables and the log odds of having symptomatic SARS-CoV-2 infection will be assessed, and the continuous variables will be modified into categorical variables if necessary. The overall fit of the final multivariate logistic regression model will be assessed with Hosmer and Lemeshow goodness-of-fit test [30], as matching might incur matching-related bias from the cases and controls having similar exposure, thus underestimating the aVE. We will also perform conditional logistic regression as a sensitivity analysis for measuring the aVE estimation against symptomatic SARS-CoV-2 infection or our primary objectives [31,32]. Furthermore, for the analysis of the Omicron period, we will perform an additional analysis of relative VE (rVE) by comparing recipients of one booster dose to recipients of the 2 doses who were eligible to receive the booster dose. The rVE will be calculated using the formula rVE = [(aVE from booster dose – aVE from 2 doses and eligible for booster)/(1 – aVE from 2 doses and eligible for booster)] × 100%. For the rVE analyses, we will include only people whose last booster dose was within 7 to 90 days before their index test date and compare them to people whose last 2-dose vaccination date was ≥90 days before their index test date [24].

This study will also conduct subgroup analyses based on the time between the last vaccination date and test index date to assess for waning of immunity (Table 2). These subgroup analyses will be conducted separately for each wave and vaccine brands or regimens. Similar to the main analysis, each vaccinated subgroup will be compared to unvaccinated people.

**Table 2 table2:** Subgroup analysis based on time since last vaccination.

Subgroup	Description
1	7-14 days between the last vaccination dose and index test date
2	14-28 days between the last vaccination dose and index test date
3	28-56 days between the last vaccination dose and index test date

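### Pfizer, Moderna and AstraZeneca boosters are analysed without regard to the primary series, so booster aVE is an unreported mixture, and rVE and booster-brand contrasts can be confounded by it

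*Protocol article*

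**What the plan says.** Study Variables sets four exposure levels, "classified as unvaccinated, dose 1 or partial vaccination, dose 2 or primary vaccination, and booster dose", and states that for vaccinated people "we will only consider the last vaccination data entry that happened before" the index RT-PCR date. Statistical Analysis says that within each wave the study will "analyze each vaccinated person separately by their vaccine brand or platform and vaccination doses, such as dose 1, dose 2, or booster", each group being compared with the unvaccinated.

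Mixed schedules are handled only up to dose 2: Study Participants excludes people "who received different vaccines for dose 1 and dose 2 or a heterologous primary vaccine series". No rule covers a change of vaccine between dose 2 and the booster.

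Study Design and Setting (text after Figure 1) reports that "these inactivated COVID-19 vaccines were only approved as boosters for patients who received similar vaccine platform for their primary vaccination regimen", and contrasts this with Pfizer, Moderna and AstraZeneca, which were not limited in that way. It also says that "Coronavac-Sinovac was the earliest COVID-19 vaccine to be introduced in January 2021 and used for mass vaccinations of doses 1 and 2". The other four brands came later, and the date given for them is August 2021.

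The rVE analysis, planned for Omicron only, is described as "comparing recipients of one booster dose to recipients of the 2 doses who were eligible to receive the booster dose", with boosters 7 to 90 days and second doses at least 90 days before the index test. Nothing requires the two sides to share a primary series. The covariates listed in Study Variables (age, gender, calendar week, neighbourhood, comorbidity, occupation, reinfection) and the matching factors (age, gender, calendar week) do not include it either.

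The word *regimen* appears next to *brand* in Sample Size and in the waning paragraph of Statistical Analysis, without a definition.

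**The concern.** The plan treats a mixed dose 1/dose 2 series as a different exposure, serious enough to exclude, yet has no rule for a mixed primary/booster series. Following the stated rules, a SinoVac booster group has one primary platform, while a Pfizer, Moderna or AstraZeneca booster group can contain several, in whatever proportions the rollout produced.

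Three quantities are affected, in different ways:

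- **Booster aVE against the unvaccinated.** The unvaccinated have no primary series, so this is not confounding. The estimate averages over a mix of regimens that is not reported, and cannot be read as a property of the booster brand.
- **Contrasts between booster brands or platforms.** Two brands can differ only because different primary series lie underneath.
- **rVE.** If boosted people and two-dose comparators have different primary mixes, the estimate combines the effect of the booster with the difference between primary vaccines. This applies to a pooled rVE as well as a brand-specific one.

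The abstract's Conclusions and the Discussion present the evaluation of inactivated, viral-vector and mRNA vaccines, to inform vaccination strategy, as the study's contribution. Readers will compare the booster brands even though no listed objective does so formally.

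**Working it through.** **1. The plan's own figure.** Sample Size assumes coverage 20–90%, VE 50–90%, precision ±5 points and alpha 0.05 (taken as two-sided); matching is 1:2. With OR = 1 − VE, p0 = coverage in controls and p1 = OR·p0/(1 − p0 + OR·p0):

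cases = (1.96 × OR/0.05)² × [1/(p1(1 − p1)) + 1/(2·p0(1 − p0))].

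The worst case is p0 = 0.20 and VE = 50%, so p1 = 0.10/0.90 = 0.111. The bracket is 10.125 + 3.125 = 13.25, giving 5,090 cases and 15,270 people. The stated 5,000 cases and 15,000 in total are reproduced. This point does not rest on a sample-size error.

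**2. Where primary series can mix.**

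- *Inactivated boosters:* approved only after a similar-platform primary series, so no platform switch is pooled. A change of brand within the platform remains possible.
- *Delta window (1 June to 31 August 2021):* boosters went to health care workers from July 2021, 6 months after the primary series. That points back to January–February 2021, when CoronaVac is the vaccine described as available. The mix should be nearly uniform.
- *Omicron window (1 January to 2 April 2022):* if Pfizer started on 1 August 2021 with 21 days between doses, the earliest second dose is 22 August. Such a person can enter the two-dose comparator after 90 days, on 20 November 2021. Under a 6-month booster interval, the same person cannot count as boosted before 22 February + 7 days = 1 March 2022. Under a 3-month interval, the date is 29 November 2021. The article does not date the change of interval. The two sides of rVE can therefore hold different primary mixes, and the mix can move with calendar time.

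**3. Illustration. All VEs and mixes here are assumed; none comes from the documents.** Booster X has aVE 60% after CoronaVac and 75% after X. Two-dose aVE at 90 days or more is 20% for CoronaVac and 50% for X. True rVE is (0.60 − 0.20)/0.80 = 50% and (0.75 − 0.50)/0.50 = 50%, the same in both strata.

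Against a common unvaccinated group, the pooled OR is the average of the stratum ORs weighted by shares among controls. If 90% of the boosted switched, pooled aVE = 0.9 × 60% + 0.1 × 75% = 61.5%; if 50% switched, it is 67.5%. Two booster brands with identical effects in each stratum would thus differ by 6 points through the mix alone. The limits are 60% and 75%.

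The plan's formula, rVE = (booster aVE − two-dose aVE)/(1 − two-dose aVE), then gives:

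| Two-dose comparator | Its aVE | rVE, 90% switched | rVE, 50% switched |
|---|---|---|---|
| X only | 50% | 11.5/50 = 23.0% | 35.0% |
| 50/50 CoronaVac/X | 35% | 26.5/65 = 40.8% | 50.0% |
| 80/20 CoronaVac/X | 26% | 35.5/74 = 48.0% | 56.1% |
| CoronaVac only | 20% | 41.5/80 = 51.9% | 59.4% |
| Same mix as the boosted | 23% or 35% | 38.5/77 = 50.0% | 50.0% |

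The true value of 50% returns whenever both sides share the primary mix.

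**4. Cost in precision of splitting.** The formula in step 1 at VE 50%, over an assumed range of cell coverage:

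| Coverage of the cell | Cases for ±5 points | Total | Half-width with 5,000 cases |
|---|---|---|---|
| 20% | 5,090 | 15,270 | 5.0 points |
| 10% | 9,839 | 29,517 | 7.0 points |
| 5% | 19,420 | 58,260 | 9.9 points |

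**The case against.** The best defence is that the last-entry sentence only fixes which dose counts at the index date. Earlier entries cannot be discarded, because the mixed-series and dose-interval exclusions need them. *Regimen* stands beside *brand* in two places and may mean primary-plus-booster combinations, and the dataset layouts are in supplementary tables not shown here. This stands in part: a reader might infer that the plan throws away dose history or fixes pooling outright, and the text does not support that. But no stated rule turns *regimen* into primary-by-booster strata, while the rules that are stated stop at brand or platform and dose number.

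A reader might also infer that every booster aVE is confounded. It is not. Against the unvaccinated, an average over the rollout's actual mix is a reasonable real-world target, and it misleads only when a brand difference is credited to the booster.

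Nor does the plan say that rVE will be run by brand against two-dose recipients of the same brand name. The 23% row is one possible comparator, not the planned one. What remains is that the planned comparator is not tied to the primary series, so even a single pooled rVE depends on how the two mixes differ.

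Finally, the introduction dates make mRNA-primed boosted people scarce early in the Omicron window if the 6-month interval applied, so an even mix may be unrealistic. That is fair, but the illustration moves from 23% to 52% with only 10% of the boosted not having switched.

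**Conclusion.** The point holds within limits. As written, Pfizer, Moderna and AstraZeneca boosters, mainly in the Omicron period, pool people with different primary series. Their aVE against the unvaccinated is an average over an unreported mix. rVE and contrasts between booster brands can be confounded by the primary series. Inactivated boosters are not affected by platform switching, and the Delta period is hardly affected.

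The size cannot be derived from the documents. Under the assumed VEs, rVE with a true value of 50% reads anywhere from 23% to 52% (90% switched) or 35% to 59% (50% switched), and booster aVE moves by up to 15 points with the mix. These figures show sensitivity and do not estimate the bias. If VE differs little by primary series, or if the mixes are nearly the same on both sides, the distortion is small. The plan should be changed before booster results are interpreted, because the remedy uses data already held.

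**What to change.** 1. Define *regimen* for boosted people as primary brand or platform plus booster brand or platform, read from all register entries before the index test. Keep the last entry for dose number and time since dose.
2. Estimate rVE within the same primary brand or platform on both sides, by restriction or stratification.
3. Report booster aVE by platform pair where numbers allow. Elsewhere, report the primary-series mix under each booster brand and do not attribute brand differences to the booster alone.
4. Recheck the 20% coverage rule and the minimum of 5,000 cases and 10,000 controls for each cell, and state whether the rule applies to the brand or to the pair.

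The data cost is recoding. Table 1 lists vaccine name, dose and date in a register of all administered doses, and the existing exclusions already require earlier doses to be read. The statistical cost is smaller cells and wider intervals for rare pairs: about 29,500 people for ±5 points at 10% coverage and VE 50%. The article expects 400,000–900,000 people in all but gives no count per pair. Sample Size already allows pooling brands of one platform, which limits the loss.

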4	56-90 days between the last vaccination dose and index test date
5	90-180 days between the last vaccination dose and index test date
6	>180 days between the last vaccination dose and index test date

A 2-sided *P* value derived from the multivariable logistic regression analysis will be used to assess VE. Data linkage and data cleaning will be performed in Google Collaboratory with the Python programming language. Furthermore, the Statsmodel library package will be used for statistical analysis [33].

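### The definition of the previous-infection covariate contradicts itself on timing and gives no stated anchor for test-negative controls

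*Protocol article*

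**What the plan says.** Under Study Variables, the protocol article names the potential confounders, among them "presence of any comorbidities, occupation, and reinfection status". It describes the last of these as follows: "Reinfection or people with previous SARS-CoV-2 infections will be presented as a dichotomous variable". The rule for coding it is "People with a previous positive RT-PCR SARS-CoV-2 result that occurred more than 90 days after the current case", and such people "will be classified as people with a previous SARS-CoV-2 infection".

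A companion 90-day rule stands under Study Participants. It excludes "People with a positive RT-PCR test result within 90 days of the preceding index test date".

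Under Statistical Analysis, covariates are candidates and are not fixed terms: "One main logistic model will be assembled by forward inclusion, and only covariates with less than 20% missing data will be considered". Also, "Assessment for confounders and effect modifiers will be performed with the Wald test".

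Table 1 under Data Sources describes the New All Records dataset (NAR) as holding all RT-PCR tests from affiliated laboratories, with ID number, swab collection date and result.

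**The concern.** The coding rule has two faults. The first is direction: it asks for an earlier positive that is dated later than the current episode. The second is the anchor. Study Participants reserves the word *case* for people who test positive in the wave, so a rule dated from the current case does not say what date to use for a control. Neighbouring variables avoid this. Age and last vaccination are both dated from the index test, which every participant has.

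This matters because the article itself treats prior infection as a potential confounder. Prior infection can lower the chance of testing positive and may go with different vaccine uptake. If the variable in the model does not measure it, the adjusted odds ratio is not adjusted for it. A programmer who follows the sentence literally would code a future infection. One who corrects only the direction could still code the variable for cases alone.

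**Working it through.** **1. Dates implied by each reading.** The wave dates come from Study Design and Setting: 1 June to 31 August 2021 and 1 January to 2 April 2022, each 92 days inclusive. More than 90 days means at least 91 days.

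| Wave | Literal (after): earliest qualifying positive, first to last index date | Look-back (before): latest qualifying positive, first to last index date |
|---|---|---|
| Delta | 31 Aug 2021 to 30 Nov 2021 | 2 Mar 2021 to 1 Jun 2021 |
| Omicron | 2 Apr 2022 to 2 Jul 2022 | 2 Oct 2021 to 1 Jan 2022 |

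Read literally, a qualifying positive falls on the last day of the wave at the earliest, and otherwise beyond it. For Delta participants this takes in Omicron-wave infections. Such a variable arises after the outcome and says nothing about immunity at the index test.

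**2. The plan's precision target, for scale.** Sample Size gives ±5% precision, coverage 20% to 90%, VE 50% to 90%, and about 5000 cases with 10,000 controls. The check uses cases = (1.96 × OR/d)² × [1/(p1(1−p1)) + 1/(2·p0(1−p0))], with p1 = OR·p0/(1−p0+OR·p0). The most demanding corner is p0 = 0.20, OR = 0.5 and d = 0.05, so p1 = 0.111. This gives 384.1 × (10.125 + 3.125) ≈ 5090 cases and 15,270 people. The plan's figure reproduces and does not depend on this covariate. It only fixes ±5 points as the yardstick.

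**3. If prior infection is in effect unadjusted.** Let qv and qu be the prior-infection prevalence in vaccinated and unvaccinated people, and h the protection from prior infection. Then

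unadjusted OR = (1 − VE) × (1 − qv·h)/(1 − qu·h).

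The article gives none of qv, qu or h. They are assumed here: prevalence 5% to 30%, h 0.5 to 0.9. For a true VE of 50%:

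| qv vs qu | VE read at h = 0.5 | VE read at h = 0.9 |
|---|---|---|
| 5% vs 5% | 50.0% | 50.0% |
| 10% vs 20% | 47.2% | 44.5% |
| 20% vs 10% | 52.6% | 54.9% |
| 10% vs 30% | 44.1% | 37.7% |
| 30% vs 10% | 55.3% | 59.9% |

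For example, 0.5 × (1 − 0.09)/(1 − 0.27) = 0.623, so VE reads 37.7%. For a true VE of 90% the full range is 87.5% to 92.0%. Some of these shifts exceed 5 points and some do not.

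This formula covers non-adjustment only. Literal coding would also condition on a post-outcome variable, and that extra effect is not estimated here.

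**4. If the direction is corrected but only cases are coded.** No control then has the value 1. The cell is empty, the maximum-likelihood coefficient is infinite and its Wald test is uninformative. In a simulated fit of 300,000 people (assumed true VE 50%, prior infection 5% vs 20%, prior-infection OR 0.2), the coefficient was 29.6 with an SE of about 17,000 and P = 0.999. A Wald screen would probably drop such a term, which leads back to step 3. If it were kept, previously infected cases would leave the comparison while previously infected controls stayed, so OR is multiplied by (1 − a)/(1 − b), where a and b are the prior-infection shares in vaccinated and unvaccinated controls. Illustrative shares of 5%/10%, 10%/30% and 20%/10% give multipliers of 1.06, 1.29 and 0.89, so a VE of 50% reads 47%, 36% and 56%.

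**The case against.** The strongest reply is that the sentence contradicts itself and so does not set a forward-looking rule. It calls the result previous, it ends by labelling the person as previously infected, and the sentence before it speaks of people with previous infections. Three cues point backward and one word points forward. The companion exclusion also hints at a look-back. This stands: the likely intent is clear. It does not remove the need for correction, because this is the only operational definition and the companion exclusion is itself unclear about direction.

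A reader might also infer that the variable is defined only for cases and will therefore separate the model. The article does not support that as fact. Both sentences speak of people, controls have an index test date, NAR can supply their earlier results, and nothing says that controls are coded as never infected. Case-only coding is one reading of a loose anchor.

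Finally, a reader might infer that VE is biased, and in a known direction. That does not follow either. The prevalences are assumptions, the bias vanishes when they are equal and reverses when the imbalance reverses, and the covariate is only a candidate for forward inclusion.

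**Conclusion.** The definition is wrong as written and has to be corrected. It contradicts itself on timing, and it leaves the reference date for controls unstated. No other part of the article resolves either point.

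Bias in VE is possible but not shown. It needs the sentence to be coded literally or for cases only, and it needs prior infection to differ by vaccination status. Under the assumed inputs above, a true VE of 50% could read about 38% to 60% if unadjusted, against a design precision of ±5 points. The expected 400,000 to 900,000 people would not shrink a systematic error of this kind.

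**What to change.** Replace the sentence under Study Variables with: *Previous infection is a positive RT-PCR collected more than 90 days before the index test date, searched identically for cases and controls in NAR.* Name the covariate *previous infection* in place of *reinfection status*, since a test-negative control cannot be a reinfection.

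Align the 90-day exclusion under Study Participants to the same anchor and direction, so that a positive in the 90 days before the index test date excludes the person and an older one sets the covariate.

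The cost is two sentences of wording and a check that the analysis code agrees. NAR already carries ID number, swab date and result. The extract must reach back before each wave, which the article does not state. The Results section says that analysis is under way, so the definition should be settled before estimates are final. Whether the covariate is forced into every model is a separate model-building choice that this correction does not require.
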